| Number of Participants with Rationale: | We include 25 patients per group as we chose a non-inferiority design for our study. If the difference of means is less than 0.3 mmHg/min, we assumed clinical equivalence: Even if HFNCT was used as THRIVE for 30 minutes, this difference would mount to 9mmHg, less than the normal range of CO 2 in arterial blood gas analysis [6] Assuming a standard deviation of 0.35 [3], an alpha of 0.025 and a power of 80%, this calculates to a sample size of 22. Accounting for drop-outs and missing data, we include 25 patients per group, or 100 patients overall.                                                                                                                                                                                                                                          |
| Study Duration:                        | 12 months                                                                                                                                                                                                                                                                                                                                                                                                                                                                                                                                                                                                                                                                                                                                                                                                                   |
| Study Schedule:                        | March 2018 – March 2019                                                                                                                                                                                                                                                                                                                                                                                                                                                                                                                                                                                                                                                                                                                                                                                                     |
| Investigator(s):                       | PD [name], [name], [name], all at the Dept. Anaesthesia and Pain Therapy, and PD [name], Departement of Paediatrics, University Hospital, Inselspital, Bern
[name], [contact], [contact], Address Inselspital [name]                                                                                                                                                                                                                                                                                                                                                                                                                                                                                                         |
| Study Centre:                          | Inselspital Bern                                                                                                                                                                                                                                                                                                                                                                                                                                                                                                                                                                                                                                                                                                                                                                                                            |
| Statistical Considerations:            | Distribution of data will be checked using qq-plots and swilk command in stata, normal distributed data will be presented as means and standard deviation, otherwise median and interquartile range will be used. Proportions will be presented as numbers and percentage. Analytical statistics uses Mann-Whitney u-tests and Students t-test, according distribution, or ANOVA and Kruskal-Wallis for multiple groups. Each of the groups will a-priory be compared to the control group independently, without correction of multiple comparisons. Other multiple comparisons or subgroup-analyses will be performed using correction factors. Proportions will be compared by Chi-square tests or Fisher's exact test. As sensitivity analyses, we will do regression analyses, using mixed effects linear regressions. |
| GCP Statement:                         | This study will be conducted in compliance with the protocol, the current version of the Declaration of Helsinki, the ICH-GCP or ISO EN 14155 (as far as applicable) as well as all national legal and regulatory requirements.                                                                                                                                                                                                                                                                                                                                                                                                                                                                                                                                                                                             |

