| Background and Rationale: | 
After induction of general anaesthesia apnoea sets in. To ensure ventilation a tracheal intubation is then performed. If no measures to ensure ventilation are taken, desaturation will set in within minutes. To prolong the time to onset of desaturation pre-oxygenation is applied beforehand. Also, preparations to ensure swift tracheal intubation are made. Nevertheless, there is a phase, in which the patient is apnoeic, and deoxygenation may occur.
 
However, if anaesthesia needs to be provided in emergency situations or in the presence of a difficult airway, the rate of complication increases rapidly [1]. In these circumstances methods that reduce desaturation incidents during prolonged difficult intubation are desirable.
 
High-Flow nasal cannula therapy (HFNCT) is the administration of heated, humidified air/oxygen via nasal cannulas at rates of 50-100l/min. HFNCT was developed in intensive care unit as an alternative to continuous pressure support (CPAP). A new application for HFNCT in adults is the extension of apnoea time in patients with difficult airways who are undergoing general anaesthesia [2]. In this environment, a new term for this kind of oxygen therapy was created: THRIVE - transnasal humidified rapid-insufflation ventilatory exchange. Using HFNCT with continuous laryngoscopy, Patel et al. [2] demonstrated in fact a ventilatory effect with HFNCT.
 
THRIVE is thought to have a ventilatory effect, because slower than expected increase in <math>p\text{CO}_2</math> has been described [2, 3]. In these studies, researches compared their data to studies from the 1950-ies, where <math>\text{CO}_2</math> increase during apnoea was investigated [4, 5]. However, technology as well as patient factors have changed since then, and no study has ever directly compared different flow rates and the effect on <math>\text{CO}_2</math> clearance. Our previous research showed, that the claimed ventilatory effect is absent in children (Riva et al., British Journal of Anaesthesia, 2018, in press). Therefore, we want to systematically examine the <math>\text{CO}_2</math> clearance and possible influences in adults, and to determine, if a ventilatory effect is present at all.
 
This study investigates under controlled circumstances the concept of THRIVE to prolong the apnoea time without deoxygenation and to improve safety of airway management in patients. Furthermore, this study enables to quantify the physiologic effects of different flow rates of oxygen on carbon dioxide elimination in apnoeic patients as well as the effect of elevated <math>\text{CO}_2</math> levels on cerebral perfusion and other vital parameters.
 |

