
|                      |                                                                                                                                                                                                                                                                                                                                                                                                                                                                                                                                                                                                                                                                                                                                                                                                                                  |
|----------------------|----------------------------------------------------------------------------------------------------------------------------------------------------------------------------------------------------------------------------------------------------------------------------------------------------------------------------------------------------------------------------------------------------------------------------------------------------------------------------------------------------------------------------------------------------------------------------------------------------------------------------------------------------------------------------------------------------------------------------------------------------------------------------------------------------------------------------------|
| Objective(s): | 
This study compares under controlled conditions if different flow rates affect apnoea time after induction of anaesthesia and how CO2 clearance is influenced. Furthermore, this study enables to quantify the effects of increased pCO2 on cerebral perfusion.
 
Our primary hypothesis states that any of the three intervention is non-inferior to HFNCT regarding clearance of CO2 (ventilatory effect).
                                                                                                                                                                                                                                                                                                                                                                        |

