THRIVE has shown to be a suitable method to prolong apnoea with stable O2 saturation [2, 3]. Despite promising pilot results with high-flow nasal cannula therapy, it is unknown whether this technique is superior to low-flow nasal cannula therapy. Especially the claimed ventilatory effect has not yet been provided with sufficient data. It is thought to happen through turbulences caused by the high flow, that continue down through the trachea into the alveoli. This turbulence is said to wash out CO2 because slower increase of CO2 has been described using THRIVE vs. normal apnoea. However, this data of normal apnoea was already acquired in 1959 by Frumin et al. on only 8 healthy patients [4]. Since then, many things, including technology and patient factors have changed and this data therefore has only limited application today.

Especially the CO2 clearance under different flow rates has yet to be thoroughly examined. This is important, as increased CO2 can cause a multitude of effects like acidosis and altered cerebral blood flow [4, 11, 14]. Our study will also examine the effect of increasing paCO2 on cerebral perfusion using NIRS.

Furthermore, we will compare HFNCT at 70 l/min performing jaw thrust, with a group of patients, who's mouths will be opened using continuous video laryngoscopy, which is a standard procedure today for laryngeal surgery. In our study, we will only apply the minimal strength required in order to keep the airway patent, which can be visually confirmed using the video-monitor. Whether laryngoscopy compared to jaw thrust makes any difference in oxygenation or CO2 increase has yet to be examined.

This study investigates under controlled circumstances the concept of THRIVE to prolong apnoea time without desaturation. With our findings, we hope to improve airway management safety. Furthermore, this study enables us to better understand physiology behind apnoeic oxygenation and the influence of different nasal flow rates. Our study's extensive setup also allows us to measure the effects of increased CO2 on cerebral blood flow and cardiac output.

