### **3.5 Explanation for choice of comparator (or placebo)**

Our control group consists of standard of care use when using HFNCT. They will receive 70l/min using continuous laryngoscopy as it has been established by Patel et al. [2]. We will not use a placebo (which could be air (21% oxygen)) for this study, as this would lead to desaturation within a few minutes and is not standard of care.

However, HFNCT is not standard of care during anaesthesia induction as patients normally receive mask-preoxygenation, mask ventilation and tracheal intubation while the apnoea period is kept as short as possible.

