## 10. STATISTICAL METHODS

### 10.1 Hypothesis

Null hypothesis: The difference of the mean increase of  $p_{tc}CO_2$  between any of the three intervention groups and the control group is at least 0.3 mmHg/min, the control group being lower.

Primary hypothesis: the difference of the mean increase of  $p_{tc}CO_2$  between the groups is less than 0.3 mmHg/min (non-inferior margin), one-sided testing. This hypothesis was based on a small clinical pilot study that showed no differences regardless of flowrate or mouth opening (jaw-thrust vs. laryngoscopy).

Secondary outcome hypothesis: The number of patients not tolerating the apnoea time of 15 minutes is not significantly higher in any of the three intervention groups.

Secondary outcome hypothesis: no significant changes in vital parameters such as cerebral perfusion will be recorded.

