### 10.2 Determination of Sample Size

We assumed that with maximal flow of 70L O2/min and maximal mouth opening, there would be the least increase of  $p_{tc}CO_2$ /min. Patel et al. showed an increase of only 1.13mmHg using this technique [2]. However, this was  $etCO_2$  instead of  $p_{tc}CO_2$ . According to Gustafson et al., who measured  $p_{tc}CO_2$  as well as  $p_aCO_2$ , the  $CO_2$  increase was in fact 1.8mmHg/min, with a standard deviation of 0.35mmHg [3]. This correlated very well with our own findings in our pilot study (not published).

Using a non-inferiority design, a difference of means of 0.3mmHg/min, a standard deviation of 0.35mmHg/min, an alpha of 0.025 (one-sided) and a power of 80%, the necessary sample

size calculates to 22 patients per group. Therefore, we will include 25 patients in each group to account for possible drop outs. A value of 0.3mmHg/min would still only result in a difference in increase of 9mmHg in 30 minutes of apnoea time. We defined this as measurable, but still clinically acceptable, because the normal range of standard arterial pCO2 is 11mmHg (35-46 mmHg) [6].

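### The synopsis promises to settle whether any ventilatory effect exists, but the primary test only bounds how much faster CO2 rises than under the 70 l/min control

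*Protocol*

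**What the plan says.** The synopsis (Background and Rationale) gives the purpose as examining CO2 clearance in adults and "to determine, if a ventilatory effect is present at all". Its Objective(s) entry states the primary hypothesis as "any of the three intervention is non-inferior to HFNCT regarding clearance of" CO2, and a parenthesis identifies that clearance with the ventilatory effect.

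Section 10.1 sets the formal test: the difference in mean p_tcCO2 increase from the control group "is less than 0.3 mmHg/min (non-inferior margin), one-sided testing". Section 10.2 sizes it with "a standard deviation of 0.35mmHg/min" and "an alpha of 0.025 (one-sided) and a power of 80"%, giving 22 per group, raised to 25. The margin is defended there as clinically acceptable: 9 mmHg over 30 minutes, against a normal arterial range 11 mmHg wide.

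All four arms receive nasal oxygen (section 6.1): 70 l/min with laryngoscopy (control), and 70, 10 and 2 l/min with jaw thrust. Section 3.5 declines a placebo: "We will not use a placebo (which could be air (21% oxygen)) for this study", because it would cause desaturation within a few minutes. On the control's own effect, section 3.1 says that "the claimed ventilatory effect has not yet been provided with sufficient data" and attributes the presumed mechanism to turbulence from the high flow. Section 10.3.1 makes each group against control the a-priori comparison.

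**The concern.** Whether an effect exists at all is a question about treatment against its absence. Non-inferiority between active arms answers another question: whether one arm is worse than another by less than a stated amount. The control's ventilatory effect is described as unproven, the margin is not derived from any control effect over no flow, and there is no zero-flow reference. A positive result therefore leaves the synopsis question open.

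What is at stake is interpretation. A reader holding the synopsis beside a non-inferior result at 2 l/min could conclude that no ventilatory effect exists, or that 2 l/min ventilates as well as 70 l/min. The test supports neither. A second problem concerns attribution: the control differs from the 10 and 2 l/min arms in both flow and airway technique, so even a clear difference there could not be credited to flow alone.

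**Working it through.** **Inputs from the protocol.** Margin 0.3 mmHg/min, SD 0.35 mmHg/min, one-sided alpha 0.025, power 80% (sections 10.1 and 10.2); 25 per group (section 6.1). The true difference used for sizing is not given as a number. Zero is implied by the pilot, which section 10.1 says showed no differences.

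**Reproducing the plan's figure.** n = 2 × (1.960 + 0.842)² × 0.35² / 0.3² = 21.4, so 22 per group. The stated figure reproduces. With the noncentral t distribution, 22 per group gives 79.3% power and 25 give 84.4%.

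**Precision at 25 per group.** SE = 0.35 × √(2/25) = 0.0990, df = 48, t(0.975) = 2.011. The 95% CI half-width is 2.011 × 0.0990 = 0.199 mmHg/min. Non-inferiority is therefore declared when the observed difference is below about 0.3 − 0.199 = 0.101.

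**Chance of each finding by true difference d (arm minus control).** The noncentrality is (0.3 − d)/0.0990 for non-inferiority and d/0.0990 for showing that the interval lies above zero. The values of d are assumed; the protocol gives no effect size against no flow.

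| d (mmHg/min) | Declared non-inferior | CI shown above 0 |
|---|---|---|
| 0 | 84% | 2.5% |
| 0.05 | 70% | 7% |
| 0.10 | 51% | 17% |
| 0.15 | 32% | 32% |
| 0.20 | 17% | 51% |
| 0.30 | 2.5% | 84% |
| 0.50 | under 0.01% | over 99% |

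**Reading the table against the aim.**

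1. No ventilatory effect in any arm: d = 0, verdict non-inferior with 84% probability.
2. An effect of any size shared equally by all arms: d = 0 again, 84% again. The data cannot tell this from case 1.
3. An effect only at high flow and below the margin: at 0.1 the verdict is non-inferior about half the time, and the difference is shown to exceed zero only 17% of the time.
4. An effect only at high flow and at or above the margin: non-inferiority at 10 and 2 l/min becomes rare (2.5% at 0.3, practically never at 0.5).

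**What each contrast with control isolates.** For 70 l/min jaw thrust, flow is equal, so the contrast concerns airway technique only. For 10 and 2 l/min jaw thrust, flow and technique both differ. The contrasts that vary flow alone are 70 against 10 and 70 against 2 l/min, all under jaw thrust. They are not among the a-priori comparisons in section 10.3.1.

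**The case against.** A reader might infer that the verdict comes out the same whether or not the effect exists, or that the trial has no assay sensitivity at all. The documents do not support that. Section 3.1 describes a flow-driven mechanism, under which 10 and 2 l/min act as internal low-flow references, and the table shows the verdict reversing as d approaches 0.3. The verdict is blind only to an effect common to all flows, and only weakly sensitive to one well below the margin.

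Nor is the one-sided test the only planned inference. Section 10.3.1 also lists ANOVA or Kruskal-Wallis tests and mixed-effects regression, and the synopsis names EIT as a secondary outcome to validate the ventilatory effect. This stands against any claim that nothing else bears on the question. It does not rescue the synopsis aim: section 8.5.2 describes EIT for atelectasis, end-expiratory lung impedance and inhomogeneity, with no rule for concluding that ventilation occurred, and the other analyses still compare only arms that receive oxygen.

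The formal sections are also narrower than the synopsis. Section 4.1 speaks of the effect of nasal flow on CO2 clearance, and section 2.1.1 gives a practical use for non-inferiority, namely widely available and cheaper devices. That question has content even if the control has no ventilatory effect, and a clinical-acceptability margin suits it. The synopsis background also says an earlier high-flow study did demonstrate the effect, although section 3.1 calls the evidence insufficient. Finally, nothing in the protocol says a positive result will be reported as absence or equality of effect; that risk comes from the synopsis wording and is not a stated plan. These points lower the severity. The mismatch between the stated aim and the primary test remains.

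**Conclusion.** The concern holds as a mismatch between claim and test. The primary analysis can rule out a CO2 rise 0.3 mmHg/min or more faster than control. It cannot determine whether a ventilatory effect is present, absent or equal across arms. With 25 per arm and SD 0.35, non-inferiority is declared with 84% probability both when no arm has an effect and when all arms share one, and with 51% probability when a flow-dependent effect of 0.1 mmHg/min exists.

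These figures rest on the protocol's SD, full enrolment with no drop-outs, a t-test, and assumed true differences. With 22 evaluable per arm, 84% becomes 79% and 51% becomes 46%.

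The primary test is valid for the bound it states, so this is a correction of wording and reporting and not a mandatory design change. Declining a placebo is not itself the fault; the fault is keeping an aim that would need a no-flow reference.

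**What to change.** - **Synopsis, Background and Rationale:** replace the clause on presence at all with *whether the CO2 rise differs between flow rates*, in line with section 4.1.
- **Synopsis, Objective(s):** delete the parenthetical reference to a ventilatory effect from the primary hypothesis.
- **Sections 10.1 and 10.3:** state that non-inferiority is reported only as *CO2 rises less than 0.3 mmHg/min faster than control*, and not as presence, absence or equality of a ventilatory effect.
- **Section 10.3.1:** add two-sided 95% CIs for 70 l/min jaw thrust against 10 l/min jaw thrust and against 2 l/min jaw thrust. Conclude a flow-dependent effect only if the interval excludes 0; otherwise report its limit as the largest effect not excluded.

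The cost is a narrower claim and two further contrasts. The expected half-width is about 0.20 mmHg/min. Section 10.3.1 already applies a correction to comparisons other than those against control, without naming the method. If Bonferroni over the two were used, t(0.9875, 48 df) = 2.314 and the half-width becomes 2.314 × 0.0990 = 0.23. Arms, sample size, margin, primary test and patient care do not change.
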